### Intervention

#### EA combined with donepezil group

The acupoints are GV 16, GV 20, GV 24, and *Shang Yintang* (up to GV 29 1 cun), as well as bilateral EX-HN 5 and KI 4. The location of the acupoints is based on the *The Name and Location of Acupoints* drafted in 2006 by the National Standard of the People’s Republic of China (GB/T 12346-2006). The acupuncture protocol is based on reviews of acupuncture for AD [18, 19] published and expert consensus. Acupuncturists who have at least 2 years of practical experience will perform the intervention. Disposable, sterilized needles made of stainless steel (Hwato, Suzhou Medical Appliance Factory, Suzhou, China) and electric stimulators (SDZ-V electroacupuncture apparatus, Suzhou Medical Appliance Factory, Suzhou, China) will be used in the treatment group. After routine disinfection, the GV 16 will be needled while participants are in the sitting position with their head slightly forward and their muscles relaxed. The needle (25 mm in length) will be inserted obliquely and slowly downward toward the mandibular direction to a depth of 12.5 mm. The needle will be immediately removed after “*de qi*” (*de qi*, which is very important to therapeutic effect, is a sensation of soreness, heaviness, and numbness when needling [20]) and not retained. *Shang Yintang*, GV 20, and GV 24 will be needled (40 mm in length) at a 30° angle to a depth of approximately 12.5 mm while participants are in the decubitus position. For bilateral EX-HN 5 and KI 4, the needle (40 mm in length) will be vertically inserted to a depth of 25 mm. The electric stimulator will be applied to GV 20, GV 24, and bilateral EX-HN 5 with a spare-dense wave of 10/50 Hz, 0.5–5.0 mA. The current intensity is set up to the maximum tolerance of patients. There are three sessions per week with each session lasting for 30 min. There will be 12 weeks of treatment with 36 sessions for each participant in total. EA treatment will last for 12 weeks.

Donepezil (Eisai Pharmaceuticals, Shanghai, China) 5 mg will be given once daily before bed-time for the first 4–6 weeks. Based on the treatment effect, the dosage may be increased to 10 mg once daily before bed-time for the next 6–8 weeks. Donepezil will be taken for continuously for 24 weeks.

#### Donepezil group

Participants will only receive donepezil using the same administration method as with the EA combined with donepezil group and the therapy will last for 24 weeks.

Routine medications and therapies taken by participants with other complex chronic diseases will be recorded in detail in a paper Case Report Form. The intervention will be terminated due to severe adverse events.

### Outcome measures

The primary outcome is the change from baseline in the Alzheimer’s Disease Assessment Scale-cognition (ADAS-cog) [21] score measured at week 12. The maximum score of the ADAS-cog is 70 including 15 items of cognitive dysfunction assessment. The higher values indicate higher degree of deficit [22].

The secondary outcomes include the following items: the change from baseline in the ADAS-cog score measured at week 36. The change from baseline in total MMSE score [23], in the Alzheimer’s Disease Cooperative Study-Activity of Daily Living (ADCS-ADL) score, and in the Quality of Life-Alzheimer’s Disease (QOL-AD) score measured at weeks 12 and 36. The MMSE score is commonly used for estimating the severity of cognitive impairment with a maximum score of 30. The questions in this scale included orientation to time, orientation to place, attention and calculation, recall of three words, and visual construction. The ADCS-ADL score contains 19 domains about assessment of basic and operational ability of daily living [24]. The QOL-AD score, which includes physical health, mental health, social and financial assessment, and quality of life domains, is completed by both patients and caregivers [25].

All the adverse events will be recorded and assessed throughout the whole study period. Adverse reactions related to acupuncture may be fainting, hematoma formation, local infection or skin pain. Individuals who develop severe complications will be excluded from continuing in study, and the reasons for their termination will be recorded.

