## Methods/Design

This trial is a prospective, randomized controlled, clinical trial to be conducted between June 2017 and December 2019. Three hundred and thirty-four participants with AD will be recruited at Guang’anmen Hospital, Beijing, China via the hospital web or posters. Recruiting and screening will be in the charge of a research assistant, whereas the diagnosis will be made by a neurologist. A 2-week baseline assessment will be conducted. Randomization is performed by the pharmacological assessment center at Guang’anmen Hospital. The participants identified as eligible will be randomized into two groups—EA combined with donepezil and donepezil—at a ratio of 1:1. The random block is set to 4, and random grouping is produced by using the Statistics Analysis System (SAS) software. Random numbers and information about grouping are sealed into opaque envelopes with correlative sequence numbers of entering the trial marked on the outside. Acupuncturists will open the envelopes according to the sequence numbers. The flowchart of the trial is shown in Fig. 1. The total study period of this trial is 38 weeks (Fig. 1), including 2-week baseline assessment, 12-week treatment period and 24-week follow-up period.

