### Sample size and statistical analysis

The calculation of sample size is based on the primary outcome which is the change from baseline in the ADAS-cog score. According to previous studies [26], 39% of patients showed an improvement of at least 4 points on the ADAS-cog score after being treated with donepezil. We estimated the rate to be 39% in the donepezil group and 55% in the EA combined with donepezil group. Three hundred and four participants were needed to provide 80% power at a significant level of 5% using analysis of variance. The total sample size required for the study is 334 (167 each group) assuming a 10% loss to follow-up.

Baseline score of the ADAS-cog and age will be used as a covariate when assessing the differences between the EA combined with donepezil group and the donepezil group by an analysis of covariance for the primary and the secondary variables if data fits the normal distribution. Otherwise, a nonparametric test will be used to compare the statistical difference between the two groups. All the data will be blindly analyzed by the statisticians from the Clinical Evaluation Center of Guang’anmen Hospital. SPSS 20.0 (IBM Corp., Armonk, NY, USA) statistical software will be used for the statistical analyses. Subanalysis will be applied to the statistical analysis according to the severity of the condition of participants measured by the ADAS-cog [27]).

Efficiency and safety analysis will be based on all the participants at randomization according to the intention-to-treat (ITT) principle. Missing values assumed missing at random will be handled by the multiple imputation method [28]. Continuous data will be presented by the average and standard error. Two-sided tests will be used for all outcomes. A *P* value of less than 0.05 is considered to show statistical significance.

For the safety assessments, a description on the adverse events and adverse reactions will be presented in tables. These tables will include the categories, severity, rate of incidence, and correlation with the treatment. Individuals with serious adverse events should stop receiving the intervention and details will be reported in a timely manner.

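### As worded, the rule on severe complications takes patients out of the study rather than off treatment, creating avoidable missing outcomes at weeks 12 and 36

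*Protocol article*

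**What the plan says.** The protocol article gives the consequence of a serious harm in three places.

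- Outcome measures, last paragraph, after the list of possible acupuncture reactions: "Individuals who develop severe complications will be excluded from continuing in study, and the reasons for their termination will be recorded".
- Intervention, Donepezil group: "The intervention will be terminated due to severe adverse events".
- Sample size and statistical analysis, last paragraph: "Individuals with serious adverse events should stop receiving the intervention".

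The first removes the patient from the study. The other two stop the treatment and do not mention leaving the study.

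Three further statements bear on the point. On the analysis set: "Efficiency and safety analysis will be based on all the participants at randomization according to the intention-to-treat (ITT) principle". On gaps in the data: "Missing values assumed missing at random will be handled by the multiple imputation method". On safety recording, in the same paragraph as the exclusion rule: "All the adverse events will be recorded and assessed throughout the whole study period". Methods/Design fixes the length of that period: "The total study period of this trial is 38 weeks".

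The primary outcome is the change in ADAS-cog at week 12. Week 36 is a secondary time point.

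**The concern.** Stopping treatment and leaving the study are different events. A patient who stops electroacupuncture or donepezil can usually still be tested at week 12 and week 36. A patient removed from the study is not tested. The Outcome measures sentence prescribes removal, so the protocol's own rule would produce missing outcomes that need not be missing.

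Three things follow if it is applied as written.

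- Intention-to-treat analysis needs outcomes on everyone randomised. The removed patients remain in the analysis set, so who is analysed does not change. What changes is that their outcomes are imputed.
- The imputation assumes missing at random. Here the missingness is triggered by a harm. If harmed patients fare differently from patients with similar recorded data who stayed, their imputed values are off.
- Removal may be unequal between arms. The electroacupuncture arm has an extra procedure with its own complications, although donepezil reactions can trigger the rule in both arms. Unequal removal combined with wrong imputed values biases the treatment difference.

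Safety follow-up is also affected. Removing the most seriously harmed patients sits badly with recording adverse events over the full 38 weeks.

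**Working it through.** **1. The three rules side by side**

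| Section | Trigger | Consequence |
|---|---|---|
| Outcome measures | severe complications | out of the study |
| Donepezil group | severe adverse events | intervention ends |
| Sample size and statistical analysis | serious adverse events | intervention ends |

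The triggers are not defined against each other. A severe needling complication is also a severe adverse event, so the first two rows apply to the same patient and give different instructions. Nothing in the article says that assessments continue once the first row applies.

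**2. The plan's own sample size**

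Inputs from the sample size section: responder rates 39% and 55%, two-sided 5%, 80% power, 1:1 allocation. With mean rate 0.47:

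n per arm = [1.960 × √(2 × 0.47 × 0.53) + 0.842 × √(0.39 × 0.61 + 0.55 × 0.45)]² / 0.16² = 151.6, rounded up to 152.

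Two arms give 304, as stated. Adding 10%: 304 × 1.10 = 334.4, in line with the stated 334. These figures serve only as a yardstick; the point about the wording does not depend on them.

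**3. Share of the reserve**

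The plan says: "The total sample size required for the study is 334 (167 each group) assuming a 10% loss to follow-up". The reserve for all losses is 334 − 304 = 30 patients. The article gives no rate of severe complications, so I assume that 1 to 5% of one arm is removed.

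- 1%: 0.01 × 167 = 1.7 patients; 1.67/30 = 6% of the reserve.
- 5%: 0.05 × 167 = 8.4 patients; 8.35/30 = 28% of the reserve.

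**4. Power**

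On the responder calculation, power is 80.1% at 152 per arm. A 10% loss from 334 leaves about 301 patients and 79.7%. If a further 5% of all patients were lost, about 284 remain and power is 77.4%. The power cost is small.

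**5. Possible bias**

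The article gives no ADAS-cog standard deviation, so I work in SD units. The difference detectable with 152 per arm is (1.960 + 0.842) × √(2/152) = 0.321 SD.

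Bias = (excess share removed in one arm) × (gap between true and imputed mean score, in SD). Both factors are assumptions.

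| Excess share | Gap | Bias | Share of 0.321 SD |
|---|---|---|---|
| 1% | 0.25 SD | 0.0025 SD | 0.8% |
| 5% | 0.5 SD | 0.025 SD | 7.8% |
| 10% (unlikely) | 0.5 SD | 0.05 SD | 15.6% |

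The sign is open: it depends on which arm loses more patients and whether they do better or worse than imputed.

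**The case against.** The strongest reply is that the sentence is loose wording for stopping treatment. It follows a list of acupuncture reactions, and its closing reference to termination echoes the Donepezil group section, where it is the intervention that is terminated. The rules on whole-period adverse event recording and on analysing everyone randomised also fit that milder reading. This may well be what the authors meant. But the sentence names the study, not the treatment, and site staff act on what is written. If the milder reading is intended, the correction only makes the text say so.

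A second reply is that procedures after discontinuation are normally left to the full protocol. That is true of a missing detail, and the two sections that only stop the intervention would not be at fault for their silence. It does not cover a rule that the article states and that conflicts with its other two.

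A third reply is that the harm is not demonstrated, and much of this stands. The event rate, the SD and the gap are all unknown, and the bias range rests on assumptions. Removals may fall within the 10% loss allowance rather than add to it. Electroacupuncture ends at week 12, so an event after the week-12 visit costs only the week-36 data and leaves the primary outcome untouched. The mixed use of severe and serious, and of complications and events, is mainly editorial.

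**Conclusion.** The concern holds. Taken as written, the Outcome measures rule ends study participation where the rest of the article ends only treatment, and it leaves outcomes to be imputed that could have been observed. The probable effect is modest: about 2 to 8 patients, and a bias of 0.0025 to 0.025 SD in either direction, if 1 to 5% of one arm is removed and true scores differ from imputed ones by 0.25 to 0.5 SD. Those rates and gaps are assumptions. The conclusion about the wording does not rest on them, but it does depend on the sentence being applied literally. The reason to act despite the small size is that uncollected scores cannot be recovered at the analysis stage, and the article reports that recruitment is under way.

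**What to change.** In the last paragraph of Outcome measures, replace the exclusion rule with wording such as: patients with severe complications stop the intervention only; they remain in follow-up, with the week-12 and week-36 assessments and adverse event recording, unless they withdraw consent. Use the observed scores in the primary analysis and impute only what is truly missing, for example when a patient is too ill to be tested. The clinical decision to stop treatment is unchanged. As an editorial tidy-up, use one defined trigger term in all three sections.

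The cost is one sentence, its submission to the Ethics Committee as a protocol modification, and a few already scheduled visits for patients off treatment. The site will still see some of them anyway, because Ethics and dissemination offers free therapy and consultation to those harmed by participation.

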### Sample size and statistical analysis

The calculation of sample size is based on the primary outcome which is the change from baseline in the ADAS-cog score. According to previous studies [26], 39% of patients showed an improvement of at least 4 points on the ADAS-cog score after being treated with donepezil. We estimated the rate to be 39% in the donepezil group and 55% in the EA combined with donepezil group. Three hundred and four participants were needed to provide 80% power at a significant level of 5% using analysis of variance. The total sample size required for the study is 334 (167 each group) assuming a 10% loss to follow-up.

Baseline score of the ADAS-cog and age will be used as a covariate when assessing the differences between the EA combined with donepezil group and the donepezil group by an analysis of covariance for the primary and the secondary variables if data fits the normal distribution. Otherwise, a nonparametric test will be used to compare the statistical difference between the two groups. All the data will be blindly analyzed by the statisticians from the Clinical Evaluation Center of Guang’anmen Hospital. SPSS 20.0 (IBM Corp., Armonk, NY, USA) statistical software will be used for the statistical analyses. Subanalysis will be applied to the statistical analysis according to the severity of the condition of participants measured by the ADAS-cog [27]).

Efficiency and safety analysis will be based on all the participants at randomization according to the intention-to-treat (ITT) principle. Missing values assumed missing at random will be handled by the multiple imputation method [28]. Continuous data will be presented by the average and standard error. Two-sided tests will be used for all outcomes. A *P* value of less than 0.05 is considered to show statistical significance.

For the safety assessments, a description on the adverse events and adverse reactions will be presented in tables. These tables will include the categories, severity, rate of incidence, and correlation with the treatment. Individuals with serious adverse events should stop receiving the intervention and details will be reported in a timely manner.

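### The 304 participants and 80% power come from comparing responder rates (39% v 55%), not from an analysis of variance of ADAS-cog change, so the stated power is not that of the planned primary test

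*Protocol article*

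**What the plan says.** Under Outcome measures, the primary outcome is continuous: "The primary outcome is the change from baseline in the Alzheimer’s Disease Assessment Scale-cognition (ADAS-cog) [21] score measured at week 12".

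Under Sample size and statistical analysis, the article ties the sample size to that outcome: "The calculation of sample size is based on the primary outcome which is the change from baseline in the ADAS-cog score". The planning evidence it then gives is a responder proportion from an earlier study: "39% of patients showed an improvement of at least 4 points on the ADAS-cog score after being treated with donepezil". The assumed effect is also a pair of proportions: "We estimated the rate to be 39% in the donepezil group and 55% in the EA combined with donepezil group". The result is attributed to a method for means: "Three hundred and four participants were needed to provide 80% power at a significant level of 5% using analysis of variance". The allowance for loss follows: "The total sample size required for the study is 334 (167 each group) assuming a 10% loss to follow-up".

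The same section plans an analysis of covariance, adjusted for baseline ADAS-cog and age, for the primary and secondary variables. A nonparametric test replaces it if the data are not normal. On sidedness it says: "Two-sided tests will be used for all outcomes". Neither the primary nor the secondary outcomes include the proportion improving by at least 4 points.

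**The concern.** The stated basis (mean change), the stated inputs (two proportions) and the stated method (analysis of variance) do not fit together. A sample size for a comparison of mean change needs a mean difference and an SD, and the article gives neither. This is not detail left out for brevity: the paragraph gives a basis, inputs and a method, and the inputs disagree with the other two.

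At stake is what the 80% means. If it describes a responder comparison, the article gives no power for the test that will decide the trial and no target difference in ADAS-cog points. A reader of the results would then have no planned mean effect to set the estimate and its confidence interval against.

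**Working it through.** **Inputs from the article.** Rates 0.39 and 0.55, two-sided 5%, 80% power, 1:1 allocation, 304 before and 334 after the loss allowance, 10% loss.

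**Inputs not in the article (assumptions).** SD of ADAS-cog change of 5 to 8 points; a true mean difference of 2 points; normal change scores with equal SD in both arms; correlation of 0.3 to 0.5 between the covariates and the outcome.

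**1. Reproduce 304.** Two-proportion formula with pooled variance under the null and no continuity correction, mean rate 0.47:

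n per arm = [1.960 × √(2 × 0.47 × 0.53) + 0.842 × √(0.39 × 0.61 + 0.55 × 0.45)]² / 0.16²

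= [1.3834 + 0.5864]² / 0.0256 = 151.6, so 152 per arm and **304 in total**. Power at 152 per arm is 80.1%.

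Variants:

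| Method | Per arm | Total |
|---|---|---|
| Pooled, uncorrected | 152 | 304 |
| Arcsine | 152 | 304 |
| Unpooled | 149 | 298 |
| Continuity-corrected | 164 | 328 |
| Pooled, one-sided | 120 | 240 |

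The article's figure is a standard two-sided comparison of proportions.

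**2. What a comparison of means can detect with 152 per arm.** Detectable difference at 80% power, unadjusted = (1.960 + 0.842) × √(2/152) = **0.32 SD**.

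| Assumed SD (points) | Detectable difference (points) | Power for an assumed 2-point difference |
|---|---|---|
| 5 | 1.6 | 94% |
| 6 | 1.9 | 83% |
| 7 | 2.2 | 70% |
| 8 | 2.6 | 58% |

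Power is from the two-sample t test; the normal approximation differs by less than half a percentage point.

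Adjustment for covariates multiplies 0.32 by √(1 − ρ²): about 0.31 SD at ρ = 0.3 and 0.28 SD at ρ = 0.5.

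**3. What the article's own rates imply for means.** Under an equal-SD normal shift, the standardised difference is z(0.55) − z(0.39) = 0.126 + 0.279 = **0.405 SD**. Power of the unadjusted t test at 152 per arm is then about **94%**, and 97 per arm would give 80%.

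Sensitivity to equal SDs: hold the two rates and let the SD in the electroacupuncture arm run from half to twice the control SD. Power falls from about 97% to about 83%.

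**4. Loss allowance.** 304 × 1.10 = 334.4, which is the article's 334. To keep 304 after 10% loss needs 304 / 0.90 = 337.8, so 338. The loss that 334 can bear is 1 − 304/334 = 9.0%. With 10% loss, 334 × 0.90 = 300.6 remain. At 150 per arm the responder comparison has 79.6% power, against 80.1% at 152.

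**The case against.** The strongest reply is that nothing here shows harm. The only power for a test of means that uses the article's own rates is about 94%, above the stated 80%. It stays above 80% when the SD ratio between arms varies from one half to two. The lower figures, down to 58%, need both an SD and a 2-point effect that the article does not give. This stands. A reader might infer that the trial is underpowered for its primary outcome; the article does not support that.

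Two other strong readings also go too far. A reader might say that the planned effect is never tested. But the responder rate is a cut of the same ADAS-cog change, which the primary analysis tests on its continuous scale. A reader might also say that a null result could not be interpreted. But a confidence interval for the mean difference, read against a clinically relevant change, would still be informative.

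It can also be said that the loss slip is trivial, and more so because the article analyses all randomised participants and imputes missing values. The size is indeed trivial, so it is only a wording correction.

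What the reply does not remove is the mismatch. The rates can be turned into a mean shift under extra assumptions, but that calculation gives 97 per arm, not 152. So 304 did not come from it, and the label on the 80% remains wrong.

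**Conclusion.** The point holds, as something that should be fixed rather than a fault that threatens the trial. The arithmetic behind 304 is sound for two proportions, and the match is exact. The error lies in attributing the figure, and its 80% power, to an analysis of variance of the primary outcome. The power of the planned analysis of covariance is not stated and cannot be derived from the article without outside assumptions. Depending on those, it is about 94% (equal-SD normal shift from the stated rates) or anywhere from about 94% to 58% (2-point difference, SD 5 to 8 points), before any gain from covariates. Neither set of assumptions has support in the article, so no claim of too little or too much power follows.

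The loss allowance is off by four participants and about half a percentage point of power.

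**What to change.** Keep 334 participants and the primary analysis, and restate the justification:

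1. Say that 304 comes from a two-sided 5% comparison of two proportions, 39% v 55%, with 80% power, and delete the reference to analysis of variance.
2. State separately what the primary comparison of means can detect: with 152 per arm, 80% power for about 0.32 SD unadjusted. Label that figure as unadjusted and note that the detectable difference is smaller after adjustment for baseline ADAS-cog and age. Convert it to ADAS-cog points with an SD of change that the sponsor takes from a cited source.
3. Restate the loss allowance as 9%, or note that 10% would require 338.
4. Optionally, add the week-12 rate of improvement by at least 4 points as a secondary analysis.

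Items 1 to 3 change wording only and add no participants. Item 4 uses data already collected, but it costs one more secondary test. It is also a protocol modification, so it should go to the ethics committee and be settled before unblinding. The inconsistency is cured without it.

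### The 334 to be randomised does not leave the required 304 after the stated 10% loss; it covers about 9%, a minor slip in the inflation step

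*Protocol article*

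**What the plan says.** The sample size paragraph of the protocol article (Sample size and statistical analysis) builds the number in three steps.

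- It assumes responder rates, a response being an ADAS-cog improvement of at least 4 points: "We estimated the rate to be 39% in the donepezil group and 55% in the EA combined with donepezil group".
- It gives the number needed before any loss: "Three hundred and four participants were needed to provide 80% power at a significant level of 5% using analysis of variance".
- It adds an allowance for loss: "The total sample size required for the study is 334 (167 each group) assuming a 10% loss to follow-up".

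Methods/Design repeats the final total ("Three hundred and thirty-four participants with AD will be recruited") and sets the allocation "at a ratio of 1:1". The Abstract gives the same total. On the direction of the tests, the statistical section says: "Two-sided tests will be used for all outcomes".

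The article does not show how it got from 304 to 334. The same section plans an intention-to-treat analysis of everyone randomised, with multiple imputation of missing values under a missing-at-random assumption.

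**The concern.** An allowance for loss is meant to leave the required number once the expected share of participants has gone. That calls for dividing by one minus the loss rate. Multiplying by one plus the loss rate gives a smaller total and always falls short, because (1 + d)(1 − d) = 1 − d² is less than 1.

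The three printed figures (304 required, 10% lost, 334 randomised) cannot all hold. Anyone who checks the sample size, or compares actual attrition with the allowance, would take 10% as the loss the trial can bear with 304 intact. On the article's own figures the limit is lower. What is at stake is the accuracy of that statement, and a handful of participants.

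**Working it through.** **Inputs, all from the protocol article.** Responder rates 0.39 and 0.55; significance level 5%, two-sided; power 80%; 1:1 allocation; 304 required; 10% loss; 334 randomised (167 per group).

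**1. Reproduce the 304.** The pooled-variance formula for two proportions, without continuity correction, is

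n per arm = [z(0.975) × √(2 p̄(1 − p̄)) + z(0.80) × √(p₁(1 − p₁) + p₂(1 − p₂))]² / (p₂ − p₁)²

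with p̄ = (0.39 + 0.55)/2 = 0.47.

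- First term: 1.960 × √(2 × 0.47 × 0.53) = 1.960 × √0.4982 = 1.383.
- Second term: 0.8416 × √(0.2379 + 0.2475) = 0.8416 × √0.4854 = 0.586.
- n = (1.383 + 0.586)² / 0.16² = 151.6 with unrounded terms, so 152 per arm and 304 in total.

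This matches the printed figure. Other versions give 149 per arm (298) with unpooled variance, 152 per arm (304) with the arcsine transformation, and 164 per arm (328) with continuity correction. The article names analysis of variance and no two-proportion formula, so the pooled formula is identified only by the match, and the arcsine version gives the same total.

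**2. Reproduce the 334.**

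- Multiplying: 304 × 1.1 = 334.4 and 152 × 1.1 = 167.2. Rounded, these are the printed 334 and 167.
- Dividing: 304 / 0.9 = 337.8, so 338; per arm 152 / 0.9 = 168.9, so 169.

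Only multiplication gives the printed pair.

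**3. Apply the stated loss to 334.**

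- 334 × 0.9 = 300.6, or 150.3 per arm. That is 3 to 4 participants short of 304.
- Largest loss that keeps 304: 1 − 304/334 = 30/334 = 9.0%.
- Check on 338: 338 × 0.9 = 304.2.

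This step does not depend on how 334 was reached or on which test the 304 belongs to.

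**4. Power for the responder comparison, 39% versus 55%, two-sided 5%.**

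| Per arm | Situation | Pooled | Unpooled |
|---|---|---|---|
| 152 | the required 304 | 80.1% | 80.8% |
| 150.3 | 334 less exactly 10% | 79.7% | 80.4% |
| 150 | the same, in whole participants | 79.6% | 80.3% |
| 167 | all 334 with complete data | 83.7% | not computed |

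The pooled figures after a 10% loss lie 0.3 to 0.4 percentage points below 80% and round to it. The difference in the number randomised is 338 − 334 = 4, or 4/338 = 1.2%.

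**The case against.** The strongest case on the other side is that nothing of consequence follows, and most of it stands.

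- *Power.* A reader might infer that the trial misses its own 80% power. The documents do not support that. They state power as a whole percentage, and 79.6% to 79.7% rounds to it. The sign of the gap also depends on a formula the article does not name: with unpooled variance, power after the full 10% loss is 80.3% to 80.4%. The unpooled formula would have asked for 298 rather than 304, so it is probably not the one used, but this shows how little separates the figures.
- *Analysis set.* The planned analysis keeps everyone randomised and imputes missing values, so it is not cut to 300 people. This softens the point without removing it. Imputation under missing at random does not fully restore the information lost with missing outcomes, and a loss allowance only makes sense if loss is expected to cost something.
- *Which test.* These power figures belong to the responder comparison behind the sample size. The planned primary analysis is an analysis of covariance of the change in ADAS-cog score. The article gives no mean difference or standard deviation for it, so its power cannot be computed, and no shortfall in the power of the actual primary test has been shown. That mismatch is a separate matter.
- *Inference.* The multiplication is read off the numbers and is not stated. This is granted, but the disagreement between 304, 10% and 334 remains however 334 was obtained.
- *Condensed article.* Nothing is claimed to be missing. The three figures are printed and do not fit together.

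**Conclusion.** The inconsistency is real and minor. At the stated 10% loss, 334 randomised leaves about 300 participants with complete data, 3 to 4 fewer than the 304 said to be needed; 338 would have kept 304. As printed, 334 supports a loss of about 9.0%. The likely cause is an allowance added by multiplying by 1.1.

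The head-count result rests only on the three printed figures. The power result (79.6% to 79.7%) rests on the assumed rates, a two-sided 5% test, the pooled formula that reproduces 304, and treating lost participants as contributing nothing. It gives no ground for saying that the trial is underpowered. The point merits the lowest severity, as a correction to one sentence.

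**What to change.** Keep 334 and reword the loss sentence in the sample size paragraph in one of two ways:

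- say that 334 (167 per group) leaves 304 after a loss of about 9%; or
- keep the 10% assumption and say that it leaves about 300 participants (150 per arm) with complete data.

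The second keeps the planning assumption on loss as it was made. There is no need to print a power figure to a decimal place, since it would describe the responder comparison and not the planned analysis of covariance.

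The cost is one sentence, with a slightly less favourable loss allowance or count of complete data. Enrolment, design and analysis do not change, and the total in the Abstract and in Methods/Design stays as it is.
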